### Sample size

The sample size is based on the expected difference (Cohen’s d = 0.50) on the primary outcome variable between the experimental and control group at 12 months follow-up (based on a meta-analytic review [46]). With an alpha of 0.05 and a power of 0.80 of a two-tailed test, 64 participants will need to be included in each condition. The data will be analyzed according to the intent-to-treat principle. Multiple imputations will be used for missing observations at follow-ups. We intend to increase the sample size by 25% to compensate for dropout and potential loss of power due to clustering of data, resulting in 160 participants (80 in experimental condition and 80 in control condition).

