The current study combines indicated prevention and selective prevention [44], which respectively refer to the prevention provided to adolescents with elevated levels of depression or anxiety and to the prevention provided to targeted subgroups distinguished by specific traits, in our case children who have parents with elevated levels of depression or anxiety. As mentioned above, these adolescents have an extra high risk to develop a depression or anxiety disorder. The adolescents allocated to the experimental group will undergo a preventive intervention that consists of six weekly meetings of 90 minutes each. It will focus on acquiring knowledge of depression and anxiety, learning to recognize and distinguish emotions, dealing with difficult situations, solving social problems, and creating and using a supportive social network. Throughout the program, the adolescents will complete various exercises based on cognitive behavioral therapy, behavioral activation, and exposure.

The primary aim of this study is to test the effectiveness of the program ‘Een Sprong Vooruit’ [A Jump Forward] in preventing depressive and anxiety symptoms among adolescents with elevated symptoms of depression and anxiety who have parents with elevated symptoms of depression and/or anxiety. The secondary aim is to determine whether response style and cognitive errors mediate and whether parental psychopathology, parenting stress, parental emotional support and parental control moderate the effectiveness of the prevention program.

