### Data analysis/statistical analysis

Data will be analyzed according to the intent-to-treat principle and will also be analyzed separately for the completers only. Multiple imputations will be used for missing observations at follow-ups. Regression analyses will be conducted to test differences in the development of depressive and anxiety symptoms between children in the intervention condition and children in the control condition. The results of the study will be reported in accordance with the CONSORT statement [45]. To investigate the mediating role of secondary outcome measures, such as response style and cognitive errors, mediation analyses will be performed in Mplus using bootstrap methods.

Possible baseline differences between the two conditions in demographic variables, depressive symptoms, and anxiety symptoms will be checked. Moreover, variables that show different distributions between the two groups will be entered as confounders in all models testing the effectiveness of the intervention.

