### Strengths and limitations

The strength of the study is that it will conduct follow-up assessments at 12 months in addition to 6 months in both the intervention group and the control group. This will provide the opportunity to evaluate the long-term effects of this prevention program. Additional strength of the study is that in contrast to the most RCT studies, we will focus not only on the effectiveness of the program, but also on the mediators of change (i.e., how the intervention works). Finally, the prevention program will consist of only six sessions; therefore, we expect a low dropout rate.

This study also has limitations. We will not include a placebo intervention group, limiting the extent to which decreased depression and anxiety symptoms in the intervention group can be uniquely ascribed to the prevention program. Another study limitation is its selective design. It will enable a possible labeling or stigmatization effect, which can occur during the process of identification and participation of adolescents at risk in the prevention program.

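### The sample size section expects clustering, but the planned regression names no way to account for it, and one unsplit 25% margin covers both dropout and clustering

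*Protocol article*

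**What the plan says.** All references are to the protocol article.

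- **Sample size.** The calculation is based on a standardised difference of 0.50 "on the primary outcome variable between the experimental and control group at 12 months follow-up". "With an alpha of 0.05 and a power of 0.80 of a two-tailed test", it concludes that "64 participants will need to be included in each condition". The authors then intend to "increase the sample size by 25% to compensate for dropout and potential loss of power due to clustering of data", which gives 80 per arm and 160 in total.
- **Data analysis/statistical analysis.** "Regression analyses will be conducted to test differences" between the arms in how depressive and anxiety symptoms develop. The section also names intention-to-treat and completer analyses, multiple imputation, bootstrap mediation in Mplus, and the entry of variables found to be unbalanced at baseline. It does not mention clustering.
- **Recruitment.** Eligible students are randomised individually.
- **Background and The program.** The intervention is six sessions, described in the Background as "six weekly meetings of 90 minutes each". Neither section says whether they are held in groups, or of what size.
- **Strengths and limitations.** Because the programme has only six sessions, "therefore, we expect a low dropout rate". No figure is given.

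**The concern.** The two sections do not match. One treats correlated data as likely enough to enlarge the trial. The other describes the analysis in some detail, down to software and a resampling method, without a random effect, a robust standard error or any other device for that correlation. Recruiting more participants offsets a loss of power. It does nothing for a standard error computed as if observations were independent. If outcomes are correlated within delivery groups and the model ignores this, the confidence interval for the primary comparison is too narrow and the false-positive rate exceeds 5%.

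The second part concerns the margin. One figure serves two purposes with no split, so a reader cannot tell how much clustering the trial can absorb once dropout has taken its share.

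**Working it through.** **Inputs from the article:** d = 0.50, two-sided alpha 0.05, power 0.80, 64 per arm before and 80 per arm after the increase.

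**Assumptions (not in the article):** the programme is delivered in groups of m = 8; only the intervention arm is clustered; ICC is 0.02, 0.05 or 0.10; dropout is 0% to 20%.

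**1. The plan's own figures.** A two-sample t-test needs 63.8 per arm, so 64, with power 0.801. Then 64 × 1.25 = 80. Both figures reproduce.

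**2. What dropout takes.** 80 × (1 − 0.20) = 64, so 20% dropout uses the whole margin. With 80 retained per arm and no clustering, power is 0.88.

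**3. Type I error if clustering is ignored.** The design effect in the intervention arm is DE = 1 + (m − 1) × ICC. With the other arm unclustered, the variance of the difference is multiplied by F = (1 + DE)/2. The actual error is about 2 × P(Z > 1.96/√F).

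| ICC | DE | F | 1.96/√F | Type I error |
|---|---|---|---|---|
| 0.02 | 1.14 | 1.07 | 1.89 | 5.8% |
| 0.05 | 1.35 | 1.175 | 1.81 | 7.1% |
| 0.10 | 1.70 | 1.35 | 1.69 | 9.2% |

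Over groups of 5 to 10, ICC 0.01 to 0.10 and dropout 0% to 20%, the range is 5.2% to 10.4%.

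**4. Power when clustering is allowed for.** Retained n = 80 × (1 − dropout), m shrinks in proportion, and effective n = retained n / F. For 5% dropout and ICC 0.05: n = 76, m = 7.6, DE = 1.33, F = 1.165, effective n = 65.2, power 0.81.

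| Dropout | ICC 0.02 | ICC 0.05 | ICC 0.10 |
|---|---|---|---|
| 0% | 0.86 | 0.83 | 0.77 |
| 5% | 0.84 | 0.81 | 0.76 |
| 10% | 0.82 | 0.79 | 0.74 |
| 15% | 0.80 | 0.77 | 0.72 |
| 20% | 0.78 | 0.75 | 0.70 |

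**5. Largest ICC that keeps power at 0.80.** Setting effective n to 63.77 gives ICC = 2 × (n/63.77 − 1)/(m − 1).

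- 0% dropout: 2 × 0.2545/7 = 0.073
- 5%: 2 × 0.1918/6.6 = 0.058
- 10%: 2 × 0.1291/6.2 = 0.042
- 15%: 2 × 0.0664/5.8 = 0.023
- 20%: 2 × 0.0037/5.4 = 0.001, in effect none

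Groups of 8 would mean only 80/8 = 10 delivery groups. Both tables use approximations that ignore this small number, so they are slightly optimistic.

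**The case against.** Four points can be made for the plan.

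- **Silence is not an error.** Regression is a broad word that does not exclude multilevel models or robust standard errors, and a fuller protocol or SAP may specify one. This stands as far as it goes: the article does not show that clustering will be ignored. The mismatch between the two sections remains, because the article raises clustering itself and then describes its analysis without it.
- **Group delivery is not documented.** This stands. If the clustering in mind is by school, individual randomisation means that shared school membership alone need not inflate the standard error of the treatment contrast. The type I error figures therefore depend on group delivery.
- **The margin may be enough.** A reader might infer that the stated power fails whenever data cluster, or that the margin has been counted twice. The article supports neither. The 20% dropout is an assumption, the authors expect low dropout, and with low dropout there is room for modest clustering. One allowance openly given for two purposes is pooled, not double counted.
- **Dropouts are not a total loss.** CDI 2 is measured at every assessment, and multiple imputation can use the earlier scores. If their correlation with the 12-month score is 0.5 to 0.7 (assumed), 20% missing leaves an effective n of 64/(1 − 0.25 × 0.2) = 67 to 64/(1 − 0.49 × 0.2) = 71 per arm, and power of about 0.82 to 0.84 before clustering. This also stands. The gain is modest.

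**Conclusion.** The point holds in a limited form. The sample size section anticipates clustering, and the analysis section states no means of handling it. If delivery is in groups and the regression ignores this, the nominal 5% test would run at about 6% to 9%, assuming groups of 8, ICC 0.02 to 0.10 and clustering in the intervention arm only.

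The shared margin is not shown to be inadequate. It would be exhausted by 20% dropout, counting each dropout as fully lost. At 5% to 10% dropout it absorbs an ICC of about 0.06 to 0.04. An ICC of 0.10 takes power below 0.80 at any dropout rate. Which case applies cannot be told, because the dropout rate, ICC, cluster size and source of clustering are not given.

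**What to change.** **In Data analysis/statistical analysis:**

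- Name the source of clustering and a model that matches it. If the programme is delivered in groups, use a partially nested mixed model: a random effect for delivery group in the intervention arm, controls as singletons, and small-sample degrees of freedom.
- Make the imputation respect the same structure.
- Adjust the primary model for baseline (T0) CDI 2 whether or not the arms differ on it. This can win back precision without more participants, since it multiplies the variance by about 1 − r², with r the baseline to 12-month correlation. Offsetting F = 1.175 needs r² = 1 − 1/1.175 = 0.149 (r about 0.39); offsetting F = 1.35 needs r² = 0.259 (r about 0.51). The article does not give r.
- Record delivery group and school for each participant at the time of delivery, as they may be hard to reconstruct later.

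**In Sample size:** state the assumed dropout, ICC and cluster size separately, and restate the power that 160 participants give.

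**Cost:** some wording and two recorded variables, with no extra participants. Intervals may be slightly wider and the stated power may be less favourable.

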### The program

‘Een Sprong Vooruit’ [A Jump Forward], which consists of 6 sessions, each 90 minutes long. In the first session, the participants will learn about emotions, anxiety, and depression and their experiences with their parent’s mental health problem. The adolescents learn about emotions they experience, and they will learn to recognize them. During this program, they will use a schedule to examine the relations among activating events, beliefs, emotional consequences and behavioral consequences. In the second session, the adolescents will learn about the relationship between activating events, beliefs, and emotional consequences. Beliefs can be optimistic or pessimistic and play a major role in the emotional consequences. The adolescents in the study will learn to recognize pessimistic beliefs. In the third session, adolescents will be taught several strategies to replace the pessimistic beliefs with optimistic beliefs. They will learn to recognize the (negative) pattern of their beliefs, replace them, and prove that the alternative belief is true. In the fourth session, adolescents will learn that in some situations, the beliefs cannot be replaced or changed and that they have to change their behavior to influence the emotional consequences. Therefore, the assignments will comprise both pleasant and less pleasant activities. Furthermore, they will learn to organize and structure large tasks. In the fifth session, the adolescents will learn about anxiety and the development of fear over time. By means of exposure, they will learn to divide fearful activities into small steps, practice those steps, and experience the decrease in anxiety. In the sixth and last session, the fearful tasks will be evaluated and practiced again. Furthermore, the adolescents will learn that social support sometimes makes things easier. They will practice asking people in their social environment for help. Finally, the adolescents will take a look at the future and talk about how they can influence it.

### Study outcome measures

For an elaborate overview of study outcome measures, see Table 1.

**Table 1 T1:** Overview of assessments

	**Screening**	**T0**	**T1**	**T2**	**T3**	**T4**	**T5**
**Adolescent**							
Depression (CDI 2)	X	X	X	X	X	X	X
Anxiety (SCAS)	X	X	X	X	X	X	X
Suicidal ideation (CDI 2)	X	X	X	X	X	X	X
Response style (CRSQ)		X	X	X	X	X	X
Cognitive errors (CNCEQ-R)		X	X	X	X	X	X
Relational support (RSI)		X			X		X
**Parent**^ **1** ^							
Parental psychopathology (BSI)		X					
Parenting stress (OBVL)		X			X		X
Child depression (CDI 2 P)		X			X		X
Child anxiety (SCAS-P)		X			X		X

^1^Both parents will complete the questionnaires. Only parents who have absolutely no contact with children will be excluded.

### Screening measures

To assess the eligibility to participate, students will be screened for depressive and anxiety symptoms and suicidal ideation using the Children’s Depression Inventory 2 (CDI 2) and Spence Children Anxiety Scale (SCAS). Furthermore, students will be asked to complete some questions about parental psychopathology.

### Primary outcome measure

*Depression* in children and adolescents will be measured with the CDI 2 [47]. The CDI 2 contains 28 items, each consisting of three statements graded in severity from 0 to 2. This instrument has good internal consistency and convergent validity [48].

### Secondary outcome measures

*Anxiety* will be measured with the SCAS [49]. This 44-item self-report questionnaire rates the frequency of symptoms on a 4-point scale ranging from “never” to “always”. The scale has demonstrated high internal consistency, high concurrent validity, and adequate test-retest reliability across both child [50] and adolescent [51] samples.

*Suicidal ideation* will be measured with the suicide item of the CDI 2 [47], with scores of 0 (“no suicidal ideation”), 1 (“thoughts of wanting to kill oneself, with no intent to do so”), and 2 (“a desire to kill oneself, if given the chance”). Participants with a score of 2 will be excluded from the study and referred to a therapist within an institute of mental health care or a general practitioner.

*Response style* will be measured with the Children’s Response Style Questionnaire (CRSQ) [52]. This questionnaire consists of three subscales: ruminative response, distracting response, and problem solving. Items are rated on a 4-point scale ranging from “almost never” to “almost always”. The scale has moderate levels of internal consistency.

*Negative cognitive errors* will be measured with the Children’s Negative Cognitive Errors Questionnaire – Revised (CNCEQ-R) [53], which divides negative cognitive errors into five error categories, namely ‘overgeneralizing’ , ‘personalizing’ , ‘selective abstraction’ , ‘threat conclusion’ , and ‘underestimation of the ability to cope’. Items are rated on a 5-point scale from “not at all like I would think” to “almost exactly like I would think”. The questionnaire is a revised version of the CNCEQ, which has a good internal consistency and test-retest reliability [54].

*Parental emotional support* and *parental control* will be measured respectively with ‘Warmth versus Hostility’ and ‘Respect for Autonomy versus setting limits’ , which are two subscales of the Relational Support Inventory (RSI) [55]. Both subscales have six items rated on a 5-point scale ranging from “very untrue” to “very true”. The reliability varies from low to moderate.

*Parental psychopathology* will be measured with the Brief Symptom Inventory (BSI) [56]. The BSI is a short version (53 items) of the Symptom Checklist-90 (SCL-90) [57] divided into 9 symptom dimensions: Somatization, Obsessive-compulsive symptoms, Interpersonal sensitivity, Depression, Anxiety, Hostility, Phobic anxiety, Paranoid ideation, and Psychoticism. Items are rated on a 5-point scale from “not at all” to “extremely”. Both international [58] and national studies [59] showed that the questionnaire has good psychometric properties.

*Parenting stress* will be measured with the Opvoeding Belasting Vragenlijst (OBVL) [Parenting Stress Questionnaire] [60]. It is used to determine how parents experience their child, how they interact with their child, and how they feel about their own health. The questionnaire consists of 34 items scored on a 4-point scale ranging from “not true” to “very true”. This instrument has a good reliability and satisfactory validity [60].

*Depression of the child according to the parent* will be measured with the parent report of the CDI 2 [47]. Same as the child report, this questionnaire consists of 28 items, and for each item, there are three possible answers; 0 indicating the absence of symptoms, 1 indicating mild symptoms, and 2 indicating definite symptoms. The validity of this instrument is qualified as good [48].

*Anxiety of the child according to the parent* will be measured using the Spence Children’s Anxiety Scale-Parent Version (SCAS-P) [49]. The items of the SCAS-P were formulated as closely as possible to the corresponding items of the child version of the SCAS. The parent version of the SCAS demonstrates sound psychometric properties [61].

### Data analysis/statistical analysis

Data will be analyzed according to the intent-to-treat principle and will also be analyzed separately for the completers only. Multiple imputations will be used for missing observations at follow-ups. Regression analyses will be conducted to test differences in the development of depressive and anxiety symptoms between children in the intervention condition and children in the control condition. The results of the study will be reported in accordance with the CONSORT statement [45]. To investigate the mediating role of secondary outcome measures, such as response style and cognitive errors, mediation analyses will be performed in Mplus using bootstrap methods.

Possible baseline differences between the two conditions in demographic variables, depressive symptoms, and anxiety symptoms will be checked. Moreover, variables that show different distributions between the two groups will be entered as confounders in all models testing the effectiveness of the intervention.

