**Methods/Design:**

We designed a randomized controlled trial to test the effectiveness of an indicated and selective prevention program aimed at depression and anxiety in adolescent girls. Adolescents aged between 11 and 15 years old with depressive and/or anxiety symptoms and with parents who show indicators of parental psychopathology will be randomly assigned to the experimental (N = 80) or control groups (N = 80). Participants in the experimental group will follow a preventive intervention, consisting of six sessions of 90 minutes each. All participants will complete baseline, intervention phase 1 (after session 2), intervention phase 2 (after session 4), post-intervention, 6 month follow-up, and 12 month follow-up assessments. Furthermore, parents will be asked to complete assessments at baseline, post-intervention, and 12-month follow-up. Primary outcome will be depressive symptoms. Secondary outcomes will be anxiety symptoms, suicidal ideation, response style, negative cognitive errors, parental emotional support and parental control, parental psychopathology, parenting stress and adolescents’ depression and anxiety symptoms according to the parents.

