## Discussion

This study protocol presents the design of a randomized controlled trial, which will evaluate the effect of a prevention program for depression and anxiety for adolescents with a high familial risk. The primary aim of the study will be to evaluate the effectiveness of the prevention program for depression and/or anxiety among 11-15 year old female adolescents. Our secondary aim will be to examine theoretically meaningful parent and child factors that possibly moderate or mediate the effect of the prevention program. It is hypothesized that adolescents in the intervention condition will show lower levels of depressive and anxious symptoms during the follow-up compared to adolescents in the control group without a prevention program. Furthermore, it is hypothesized that response style and cognitive errors will mediate the effect of the program and that parental psychopathology, parenting stress, parental emotional support, and parental control will moderate the effect of the prevention program.

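### The trial is sized on the CDI 2 difference at 12 months, but the analysis section does not name that contrast as the primary test, and the primary aim sets anxiety beside depression

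*Protocol article*

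**What the plan says.** One set of sections points to a single outcome at a single time.

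- Abstract, Methods/Design: "Primary outcome will be depressive symptoms. Secondary outcomes will be anxiety symptoms".
- Primary outcome measure: the CDI 2 alone. The SCAS is described under Secondary outcome measures.
- Sample size: an expected standardised difference of 0.50 "on the primary outcome variable between the experimental and control group at 12 months follow-up", followed by "With an alpha of 0.05 and a power of 0.80 of a two-tailed test, 64 participants will need to be included in each condition".

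Another set treats depression and anxiety alike, over an unspecified period.

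- Background, primary aim: to test the programme "in preventing depressive and anxiety symptoms among adolescents with elevated symptoms of depression and anxiety".
- Discussion: the primary aim is restated for depression and/or anxiety, and the hypothesis is that the intervention arm "will show lower levels of depressive and anxious symptoms during the follow-up".
- Data analysis/statistical analysis: "Regression analyses will be conducted to test differences in the development of depressive and anxiety symptoms".

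The analysis section also says that baseline variables enter the effectiveness models as confounders when they are found to be distributed differently between the arms. It does not otherwise call for adjustment for baseline CDI 2.

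**The concern.** A reader of the sample-size and outcome sections would expect one confirmatory test: CDI 2 at 12 months. A reader of the aims, hypothesis and analysis would expect depression and anxiety to be tested side by side, on their course over time. The analysis section is where this should be settled. It neither points to the contrast that was powered nor says which outcome decides whether the programme works.

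Two things are at stake. First, the and/or in the restated aim can be read as success on either outcome, which would raise the false-claim rate above the stated 0.05. Second, the stated 80% power belongs to the 12-month difference and does not automatically carry over to some other test of development. The trial is non-blinded, its outcomes are self-reported, and the Discussion foresees large-scale use if the programme works. The basis for claiming effectiveness should therefore be fixed in advance.

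**Working it through.** **1. The plan's own figure.** Inputs from Sample size: d = 0.50, two-sided alpha 0.05, power 0.80.

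- Normal approximation: n per arm = 2(1.960 + 0.842)² / 0.50² = 62.8, so 63.
- Exact two-sample t-test: 63.77, so 64 per arm, as stated. Power at 64 per arm is 80.1%.
- With the 25% increase: 64 × 1.25 = 80 per arm, 160 in total, as stated.

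This calculation is for one outcome at one time.

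**2. The sections side by side.**

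| Section | Outcome | Time |
|---|---|---|
| Abstract; outcome measures | Depression primary, anxiety secondary | Not given |
| Sample size | Primary outcome | 12 months |
| Background, primary aim | Depressive and anxiety symptoms | Not given |
| Discussion, aim and hypothesis | Depression and/or anxiety; both in the hypothesis | Over the follow-up |
| Data analysis | Both, unranked | Development, undefined |

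The first two rows together give CDI 2 at T5. The last three do not identify that contrast.

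**3. If either outcome at one time point counted, each at 0.05.**

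- Independent tests: 1 − 0.95² = 9.75%.
- Correlated tests: probability that the larger of two |z| values exceeds 1.96, by simulation with 200,000 draws. For an assumed correlation of 0.3, 0.5 and 0.7 it is 9.4%, 9.1% and 8.3%.

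**4. If that were corrected by Bonferroni.** Alpha per outcome = 0.05 / 2 = 0.025, with d = 0.50 assumed for the outcome tested.

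- Power at 64 evaluable per arm: 71.2% (t-test).
- Evaluable per arm for 80% power: 77.31, so 78. With the same 25% increase: 78 × 1.25 = 97.5, so 98 per arm, 196 in total.
- With all 80 per arm evaluable, power would be 81.5%, but that leaves nothing for dropout or clustering.

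**5. If CDI 2 at T5, adjusted for T0, is the single primary test.** Power ≈ Φ(0.50 / √[(2/64)(1 − ρ²)] − 1.96), where ρ is the assumed correlation between T0 and T5 CDI 2.

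- ρ = 0.3: 84.3%.
- ρ = 0.5: 90.4%.
- ρ = 0.7: 97.7%.

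N need not change. These values ignore clustering.

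**The case against.** The strongest reply is that the hierarchy is already there. Depression is called primary, anxiety secondary, and the sample-size section ties the primary outcome to 12 months. The aim of a joint programme may name both targets while one outcome decides. The article is also condensed, so the exact model and any multiplicity rules may sit in an analysis plan that is not shown.

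Much of this stands. The absence of a detailed model is no finding, and no passage lays down a rule that success on either outcome is enough. What remains is that stated passages disagree: anxiety belongs to the primary aim and is a secondary outcome, and the analysis sentence treats the two alike. An unseen plan could not settle this without departing from one set of passages.

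Three stronger readings are tempting, and the documents support none of them.

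- *The powered contrast is not the one tested.* Development is undefined. A regression of T5 CDI 2 on arm, or a longitudinal model that yields the T5 difference, would fit the wording.
- *Every wave is a separate chance of success.* Table 1 shows CDI 2 and SCAS at T0 to T5, five of them after baseline, but the analysis section does not say which waves are tested. With assumed correlations of 0.3 to 0.7 between outcomes and between waves, separate unadjusted tests would give error rates of about 14% to 18% for T4 and T5, and 18% to 25% for T3, T4 and T5. One group-by-time test per outcome would not produce these rates.
- *A slope test would understate the effect.* No straight-line model is stated, and the direction depends on its form. Assume differences of 0, 0.2, 0.35, 0.5, 0.5 and 0.5 SD at weeks 0, 2, 4, 6, 32 and 58. The fitted line rises by only 0.32 SD, but its intercept is 0.25, so its T5 difference is 0.57 SD. With the arms held equal at baseline, the T5 difference is 0.65 SD. Both exceed the assumed 0.50.

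**Conclusion.** The concern holds as an inconsistency about the confirmatory question. The sizing and outcome sections fix CDI 2 at 12 months. The primary aim, the hypothesis and the analysis section do not single it out and put anxiety on the same footing. The powered contrast is not identified as the primary test; it cannot be said that it will go untested.

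The size is conditional. If success on either outcome at one time point counted, the false-claim rate would be about 8% to 9% rather than 5%, for assumed correlations of 0.7 to 0.3. Correcting for two outcomes would leave about 71% power at 64 evaluable per arm, assuming d = 0.50. Larger error rates need the further assumption, not found in the document, that waves are tested one by one. The sample-size arithmetic is correct.

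**What to change.** In Data analysis/statistical analysis, state that the primary analysis is the between-arm difference in CDI 2 at T5, two-sided 0.05. Adjust it for T0 CDI 2 whether or not the arms differ at baseline, so that adjustment no longer depends on a chance imbalance. Either ANCOVA or a longitudinal model that yields the T5 contrast will do. State that SCAS and all other waves are secondary. Reword the primary aim in Background and in Discussion, and the hypothesis in Discussion, to match.

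The change is to wording only, and N stays at 160. The price is that a result on anxiety alone, or at an earlier wave, could not be claimed as confirmatory.
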